Given that the target population will be physically untrained and subjected to running-based aerobic exercise training, and that reversal of these training-induced adaptations are relatively slow in such individuals [35], the study will adopt a randomized parallel group design in each phase with a relatively larger cohort of participants to account for inter-individual variability. The duration of the training period will be six weeks. This duration was deemed adequate based on previous literature, which demonstrated that approximately four weeks (total number of sessions was between 20 and 22 during the entire protocol) elicits changes in  of 6 to 14%, oxidative enzyme activities of 35 to 50% and mitochondrial protein content of 50 to 100% in untrained and moderately trained individuals [11, 36, 37].

Phase II of testing will examine the influence of protein timing upon mediating the adaptive response to endurance exercise. Participants will be randomly assigned to a group receiving the same carbohydrate-protein mixture in Phase I, but with one group ingesting the supplement immediately post-exercise, while the second group supplementation will take place during overnight recovery in a double-blinded manner. The interaction between exercise and protein ingestion on mitochondrial protein synthesis may lie outside the acute recovery phase (over eight hours post-exercise) and under circumstances of rested mitochondrial turnover rates [8, 19]. Moreover, the provision of dietary protein prior to sleep was shown to be an effective nutritional strategy to further augment muscle protein synthesis during overnight recovery [38]. Coupled with the fact that exogenous amino acids stimulate mitochondrial synthetic response in the rested state [18], protein intake during overnight recovery may increase the adaptive response to endurance training relative to immediate feeding. Therefore, comparisons between immediate versus overnight protein ingestion (Phase II) are warranted to provide an insight into the molecular and transcriptomic responses that could extend the knowledge regarding the relationship of nutrient-exercise stimuli to mitochondria biogenesis.

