### Sample size estimation

*A priori* sample size estimation (G*power version 3.1.7, University Düsseldorf, Düsseldorf, Germany) from data in the literature similar to the proposed work [11], revealed that a total of 24 participants are required to achieve 90% power to detect a worthwhile increase in an endurance performance () of 5.3 ml · kg^−1^ and standard deviation of 3.3 ml · kg^−1^, using a two-tailed t-test for independent means with an alpha level of 0.05. Rolling recruitment of 32 participants in each phase of testing will therefore be conducted when considering an anticipated 15% dropout rate [11, 36].

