### Data analysis

The majority of data include measurements of cardiovascular and intramuscular markers of endurance training adaptations at baseline and follow-up, and thus treatments × time interactions will be explored using a general linear model with baseline included as a covariate, to account for any baseline imbalances because of regression to the mean [62]. The majority of variables in this experiment therefore involve a single comparison between two level scores, and so will not be adjusted for multiple comparisons across the different variables. Any data that require a single comparison of two means will be tested for normality using the Shapiro-Wilk test before using an independent t-test or non-parametric equivalent to examine differences between treatment arms (for example, magnitude of change in absolute and relative  between treatments). Relationships between outcome variables will be examined using a Pearson’s product-moment correlation and any meaningful associations (r ≥0.7) between baseline, and the magnitude of response to exercise training will be further explored by post-stratification of the treatment group according to baseline status. Significance will be set at ≤0.05 and all results being reported as the mean and standard error of the mean (SEM) unless stated otherwise.

Participants will be advised at the initial trial enrollment meeting to carefully consider the required investment of time and effort involved in the current project. This will be undertaken to minimize any negative impact associated with loss to follow-up, and consequently likely withdrawal can be made prior to randomization [63]. However, any unforeseen circumstances or withdrawal resulting in loss to follow-up will be documented and reported in the final trial report. In accordance, the handling of missing data subsequent to withdrawal will be primarily approached in a complete-case analysis adjustment method, while an imputation method will be considered where appropriate [64, 65].

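### The default of reporting results as mean and SEM gives neither the baseline-adjusted between-arm difference with its interval nor the spread between people

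*Protocol article*

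**What the plan says.** Four statements in the protocol article bear on this point.

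- **Reporting rule (Data analysis).** Directly after the 0.05 threshold comes "all results being reported as the mean and standard error of the mean (SEM) unless stated otherwise".
- **Analysis (Data analysis).** Outcomes measured at baseline and follow-up are analysed with a "general linear model with baseline included as a covariate". Single comparisons of two means use an "independent t-test or non-parametric equivalent to examine differences between treatment arms".
- **Design (Approach to research questions).** Each phase is a parallel-group comparison "with a relatively larger cohort of participants to account for inter-individual variability".
- **Hypotheses and target difference.** The end of the Background predicts that in Phase I protein will increase cardiovascular adaptations but not intramuscular ones. Sample size estimation takes 5.3 ml/kg as a worthwhile difference, with a "standard deviation of 3.3 ml"/kg.

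The article names no confidence interval, no adjusted difference with its uncertainty, and no SD for describing outcomes. It does not say whether the SEM belongs to raw means, change scores or adjusted means.

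**The concern.** The reporting rule does not match the quantity being estimated. The model gives one number per outcome, the baseline-adjusted difference between arms, and that number has its own standard error. A mean with SEM describes how precisely a single mean is known.

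Two questions cannot be answered from a p-value beside means and SEMs:

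- **The intramuscular half of the Phase I hypothesis.** It predicts no benefit. A p-value above 0.05 does not support that. Only an interval shows how large an intramuscular effect the data rule out, and the article gives no target difference for those outcomes that could stand in for one.
- **The 5.3 ml/kg difference.** If the result is non-significant, the reader needs to know whether 5.3 has been excluded. That is read from the limits of the interval.

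The SEM is also a poor descriptive default. It shrinks the spread between people by the square root of the arm size, and it suits badly the outcomes that the plan itself expects may need non-parametric tests.

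**Working it through.** **Inputs.** From Sample size estimation: difference 5.3, SD 3.3, two-sided alpha 0.05, 24 participants needed and 32 recruited per phase. Equal allocation is assumed, because no ratio is stated; this gives 12 to 16 per arm.

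**The plan's own figure.** The article says "a total of 24 participants are required to achieve 90% power". With d = 5.3/3.3 = 1.606, an exact two-sample t-test reaches 92.4% power with 20 participants and 96.4% with 24, so 24 is not the minimum for 90%. This is a separate matter and does not affect the present point; only the SD and arm sizes are used below.

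**Step 1: SEM against SD.** SEM = SD/√n.
- 12 per arm: 3.3/√12 = 0.95, which is √12 = 3.5 times smaller than the SD.
- 16 per arm: 3.3/√16 = 0.825, which is 4 times smaller.

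**Step 2: SEM against the uncertainty of the difference.** SE of the unadjusted difference = SD × √(2/n). The 95% half-width = t(0.975, 2n − 2) × SE.

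| Per arm | Arm SEM | SE of difference | t | 95% half-width |
|---|---|---|---|---|
| 12 | 0.95 | 1.35 | 2.074 | 2.79 |
| 16 | 0.825 | 1.17 | 2.042 | 2.38 |

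The SE of the difference is √2 times the arm SEM. The rest of the gap between SEM and half-width is the t multiplier, so these are different quantities and the ratio between them does not measure an error. Two mean ± SEM ranges that just touch (a gap of 2 SEM) correspond to p of about 0.17.

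**Step 3: the adjusted difference.** The article does not give the baseline–follow-up correlation r, nor say whether 3.3 is the SD of change or of level. If it is the SD of change, the adjusted SE is 3.3 × √((1 + r)/n). At 12 per arm this runs from 3.3 × √(1.3/12) = 1.09 at r = 0.3 to 3.3 × √(1.9/12) = 1.31 at r = 0.9. With t(0.975, 21) = 2.080 the half-widths are 2.26 to 2.73, against 2.79 unadjusted. Arm means with SEM at each time do not supply r, so this interval cannot be rebuilt from them.

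**Step 4: what a non-significant result would exclude.** On the unadjusted scale, a non-significant difference is smaller than the half-width, so its upper limit is below twice the half-width.
- 12 per arm: 2 × 2.79 = 5.59. Observed differences between 5.3 − 2.79 = 2.51 and 2.79 would be non-significant and still leave 5.3 possible.
- 16 per arm: 2 × 2.383 = 4.77, so 5.3 would always be excluded if the SD is 3.3. That stops being true once the SD exceeds 3.3 × 2.65/2.383 = 3.67, where 2.65 is half of 5.3.

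The answer therefore turns on the arm size and SD actually observed.

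**The case against.** The strongest reply has four parts.

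1. **It is a default.** The rule carries its own exception and does not bar an adjusted difference with an interval. A condensed article may leave that to the full plan. This is right as far as it goes, and it lowers the severity. But the article does state a format for results, and that stated format is open to comment.
2. **SEM is a legitimate statistic.** With n given, SD = SEM × √n, so spread is recoverable, and tests and p-values are unaffected. This stands. The adjusted interval, however, is not recoverable from arm means and SEMs alone.
3. **Inter-individual variability is cited as a reason for cohort size, with no promise to display it.** This also stands: SEM is a poor descriptor here, but it does not contradict the design section.
4. **The numerical harm is easy to overstate.** A reader might infer that the SEM overstates precision about two-fold, since in SD units at 16 per arm with r = 0.7 the SEM is 0.25 and the adjusted half-width 0.52. That sets a standard error against a 95% half-width. Like for like, the adjusted SE is √(2 × 0.51/16) = 0.2525, practically equal to the SEM. A reader might also infer error in the other direction, because an interval rebuilt from follow-up SEMs would be 0.72, about 40% too wide. That presumes raw follow-up means and an r that the article does not give; from change-score SEMs the excess is about 8% (0.56 against 0.52). The documents do not support a claim that the format misstates the answer in both directions.

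Nor do they support a forecast that most comparisons will be non-significant.

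**Conclusion.** The point holds as a reporting weakness of modest severity. The stated default gives neither the estimate from the planned model nor its uncertainty, and it does not describe the spread between people. On the protocol's SD of 3.3 and equal allocation, the reader would see SEMs of 0.95 (12 per arm) or 0.825 (16 per arm), where the interval for the unadjusted difference is ±2.79 or ±2.38. The adjusted interval depends on a correlation that the article does not give.

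The consequence is greatest for the predicted absence of an intramuscular benefit, which only an interval can support, and next for whether 5.3 ml/kg is excluded. For the latter, at the planned SD most non-significant results would exclude 5.3, but the reader needs the interval to see it.

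**What to change.** Replace the SEM clause in Data analysis with:

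*For each outcome the baseline-adjusted between-arm difference will be reported with its 95% confidence interval; arms will be described by mean and SD (or median and interquartile range if non-normal) at baseline and follow-up.*

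This needs no extra data, participants or tests. The Trial status section says that Phase I collection has started and that Phase II recruitment is still to come, so both phases can be reported this way. If a fuller plan already specifies this format, the article's sentence need only be brought into line with it.

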## Discussion

The positive effects of supplementing protein in a post-exercise feeding regimen are clearly established in acute-based investigations in promoting recovery and, albeit acutely, the adaptive response through an increase in muscle protein accretion. At present, the long-term outcomes for such nutritional strategies remain poorly understood despite the potential influence of nutrient intake in maximizing the adaptive response to exercise training. The current project aims to investigate the role of post-exercise nutrient intake composition and timing in mediating the magnitude of adaptation to endurance exercise training. This will provide novel insight regarding nutrient-exercise interactions and its potential to help and develop effective and efficient means for improving human health or performance in response to regular exercise participation.

## Trial status

The first participant was randomized on 11 December 2013. Rolling recruitment and data collection for Phase I has commenced. Phase II recruitment is forthcoming.

## Abbreviations

%BF: Percentage body fat
BIA: Bioelectrical impedance analysis
EDTA: Ethylenediaminetetraacetic acid
HR: Heart rate
PCR: Polymerase chain reaction
RER: Respiratory exchange ratio
RMR: Resting metabolic rate
RPE: Ratings of perceived exertion
*GLUT-4*: glucose transporter type 4
*HK*: mitochondrial hexokinase II
*FABPpm*: plasma membrane fatty-acid binding protein
*PDK4*: pyruvate dehydrogenase kinase 4
*PPARδ*: peroxisome proliferator-activated receptor delta
*PGC-1α*: peroxisome proliferator-activated receptor gamma coactivator 1-alpha
*SIRT1*: sirtuin 1
*AMPK*: 5′ adenosine monophosphate-activated protein kinase
*P38MAPK*: P38 mitogen-activated protein kinase
*P53*: tumor suppressor p53
*ERK1* and *2*: extracellular signal-regulated kinase 1 and 2
